## Discussion

This study will reliably document not only the factors associated with follow-up rate through an intervention package (counseling and reminders through SMS texts and phone calls) but also the cost effectiveness of the intervention package. Compliance to follow-up visits is important for better outcomes of treatment for any condition. It is equally important for children with visual problems to comply with the follow-up so that they can receive complete treatment and be prevented from going permanently blind in some cases. Different studies have shown varied results regarding the effect of these interventions. Follow-up rates have found to be improved with these types of intervention in some studies while other studies show no significant improvement with the interventions [12-17]. One intervention may work better than others in some studies. We are testing these interventions to improve the follow-up rate of pediatric patients with ocular problems. Loss or noncompliance with the scheduled follow-up visits by patients who have been advised to come for follow-up is a major issue in many areas of clinical practice. Noncompliance has been a major problem with pediatric patients undergoing treatment at the Pediatric Ophthalmology Department at BEH, where only 22% of those advised attended the follow-up. Therefore, this study is attempting to determine which intervention strategy would work better for this problem. Any intervention found effective will be applied to other departments and will be implemented as the hospital policy in the future.

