### Outcomes

The primary outcome is the proportion of children completing all 3 follow-up visits in the routine standard care group, counseling group, and reminders through SMS texts and phone call group.

The secondary outcomes include the effect of parental or guardian education status in compliance to follow-up, the visual status of the children in subsequent follow-up visits, the effect of traveling distance and cost in compliance to follow-up, and the cost-effectiveness of the intervention.

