### Independent Variables

The independent variables will include the following sociodemographic factors: gender, age, ethnicity, educational status, occupation of parent or guardian, attendant relationship with the child (of parent or guardian attending with the child), distance traveled, and cost for the travel to the hospital.

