#### Univariate Analysis

Univariate logistic regression analysis will be conducted by comparing 2 variables for each variable of interest using odds ratios (ORs) and their 95% CIs. The likelihood ratio test will be used to estimate ORs and 95% CIs for all associations of interest.

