#### Multivariate Analysis

Multivariate logistic regression analysis will be performed to adjust for the simultaneous effects of multiple factors on the outcome variable. The criteria for inclusion of factors in the multivariate analysis are to include all variables from the univariate analysis with a *P* value of .1 along with all the variables of known importance. To assess the importance of each variable included in the model, the Wald statistic for each variable will be used.

Before the multivariate analysis is conducted, the association among independent variables will be checked by a chi-square test. For independent variables having more than 2 categories, dummy variables will be created. All the variables meeting the above selection criteria will be entered one by one, starting with the highly significant factors from the univariate analysis. The overall significance of independent variables in the model will be assessed by likelihood ratio test (G statistic). Selection of the final model will be based on parsimony, biological interpretability, and statistical significance. The parameters of the logistic regression model will be estimated by the maximum likelihood method. The adjusted ORs and their 95% CIs will be computed using the estimates of parameters of the final model. The dependent variable will be dichotomous: either compliance with the follow-up instruction has increased, or it has remained changed (no difference) from before the intervention study to after it. The final model will be tested for goodness of fit by Hosmer- Lemeshow chi-square (*Χ*^2^) statistic. *P* values will be noted to assess the model fit. Imputation and intention to treat analysis will also be conducted (if required).

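### Eight sociodemographic factors are screened and selected on significance in the same data, with ordinary 95% CIs, yet the article says the factors will be documented reliably

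*Protocol article*

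**What the plan says.** The claim stands in the Discussion and, in nearly the same words, in the abstract's Conclusions: "This study will reliably document not only the factors associated with follow-up rate through an intervention package".

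Independent Variables lists the factors: "gender, age, ethnicity, educational status, occupation of parent or guardian, attendant relationship with the child", followed by "distance traveled, and cost for the travel to the hospital". That makes eight. Outcomes gives three of them formal standing as secondary outcomes: parental or guardian education, and "the effect of traveling distance and cost in compliance to follow-up", which covers two more. The other five have no stated status.

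The analysis is described in some detail:

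- Univariate Analysis: "The likelihood ratio test will be used to estimate ORs and 95% CIs for all associations of interest".
- Multivariate Analysis, entry rule: "include all variables from the univariate analysis with a *P* value of .1 along with all the variables of known importance". Qualifying variables go in one at a time, the most significant first.
- Multivariate Analysis, judging variables: "the Wald statistic for each variable will be used" for individual importance, with a likelihood ratio test for the overall significance of the independent variables. The final model is chosen on parsimony, interpretability and statistical significance.
- Multivariate Analysis, reporting: "The adjusted ORs and their 95% CIs will be computed using the estimates of parameters of the final model".

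The only multiplicity correction in the article is the Bonferroni correction for three comparisons under Sample Size.

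**The concern.** A factor reaches the final table because it looked significant in these data, and its CI is then computed as if the model had been fixed beforehand. Two problems follow. With eight factors, a chance finding somewhere in the list is much likelier than 5%. In addition, the interval of any factor that passed a P-value screen is conditioned on having looked large, so it excludes 1 too often when there is no effect. Announcing the output of such a search as reliable invites readers to take a chance association, say with occupation or travel cost, as an established determinant of follow-up. For education, distance and travel cost the matter is sharper, because these are named secondary outcomes and yet whether they stay in the final model is left partly to the data.

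**Working it through.** **Inputs.** Eight factors (Independent Variables); three of them secondary outcomes (Outcomes); screen at P of .1 (Multivariate Analysis); 95% CIs (Univariate and Multivariate Analysis). No test level for factors is written, so two-sided 5% is inferred from the CIs. All factors are assumed null.

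**The plan's own figure.** The article states no error rate for factors, so the only figure to reproduce is the total of 264. Inputs are 0.50 against 0.25, level .05/3 = .0167, and 80% power. The pooled formula is n = [z(1−α/2)·√(2p̄q̄) + z(power)·√(p₁q₁ + p₂q₂)]² / (p₁ − p₂)²:

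- [2.394·√0.46875 + 0.842·√0.4375]² / 0.0625 gives 78 per group.
- 78/0.9 gives 87, and 3 × 87 = 261, within 3% of 264.
- Taking the printed .02 literally gives 74, then 83, then 249.

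The Bonferroni level therefore belongs to the group comparisons and does not extend to the factors.

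**Independent tests.**

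- Eight factors: 1 − 0.95⁸ = 0.337, about one in three. The expected number of false factors is 8 × 0.05 = 0.40.
- The three secondary factors alone: 1 − 0.95³ = 0.143.

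**Correlated tests, no screen.** With equicorrelated normal statistics, P(max|Z| > 1.96) for eight tests is 0.300, 0.250 and 0.157 at correlations 0.3, 0.5 and 0.8. For three tests it is 0.136, 0.126 and 0.099.

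**Screened procedure.** This was simulated with three equal groups at follow-up rates of 22%, 50% and 25%, and eight null binary factors from an equicorrelated latent normal. Each factor had a univariate likelihood ratio test. Those with P < .1 entered one model with group, and Wald P < .05 was counted. Separate runs with total n of 240 or 264 agree closely:

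| Latent correlation | At least one false factor | Screened-in null factors with Wald P < .05 |
|---|---|---|
| 0 | 31% to 36% | about 46% to 52% |
| 0.3 | about 27% | about 37% |
| 0.5 | 16% to 21% | about 21% to 24% |
| 0.8 | 9% to 10% | about 11% to 12% |

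The last column is the share of CIs excluding 1 among null factors that passed the screen. A valid 95% CI would give 5%.

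**Not modelled.** Variables of known importance that bypass the screen, the judgement in choosing the final model, and factors with several categories. If dummy variables were judged one by one, there would be more tests and the rates would rise.

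**The case against.** The case against has several parts, and some of it stands.

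- *These are secondary analyses in a condensed article, and multiplicity and labelling are commonly left to the SAP.* True of the absence alone. Here, however, the article fixes a selection procedure and attaches a reliability claim to its result. That conflict is on the page.
- *The 5% level is not written, and the final model does not rest on P values alone.* Both correct. The rates above are conditional on the inferred level and on a simplified selection.
- *Not all factors need be null.* The Introduction cites a study from India in which distance and cost were major barriers. With six null factors, the independent figure is 1 − 0.95⁶ = 26.5%.
- *A likelihood ratio test is already planned.* It is, but within a model whose terms the data have chosen.
- *The sentence ties the factors to the intervention package and does not name the eight variables.* It is loosely worded. Still, these are the variables whose associations with compliance the analysis sections set out to estimate.

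A reader might also infer stronger points that the document does not support. One is that chance factors would drive hospital policy: the Discussion's policy sentence concerns interventions found effective, not factors. Another is a single false-positive rate such as one in four: that needs a moderate correlation which the article does not give. A third is that family-wise control is obligatory here: for secondary factor analyses, statisticians differ on that.

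**Conclusion.** The concern holds as a mismatch between procedure and claim. With all eight factors null and 5% inferred from the CIs, at least one false factor arises with probability 33.7% if the tests are independent, and roughly 10% to 35% under the screened procedure across assumed latent correlations from 0.8 down to 0. CIs for null factors that pass the screen exclude 1 in roughly 11% to 52% of cases over the same range. These are conditional figures, since the correlation, the binary coding and the global null are assumptions. The direction does not depend on the exact value: every scenario examined is at least about 1.8 times 5% (9/5 = 1.8). Nothing here touches the primary comparison of the three groups.

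**What to change.** 1. In Multivariate Analysis, estimate the effects of parental or guardian education, travel distance and travel cost in a model containing study group and terms set in advance, not chosen by the P of .1 screen. State whether distance and cost enter together. Use one overall likelihood ratio test per factor. Holm adjustment across the three is optional; if used, the smallest P must fall below .05/3 = .0167.
2. Label the other five factor associations (gender, age, ethnicity, occupation, attendant relationship) exploratory, reported as ORs with CIs and without significance claims.
3. In the abstract's Conclusions and the Discussion, replace the promise of reliable documentation of factors with exploratory wording.

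This needs no further patients or data. The article reports 154 of 264 enrolled as of September 2021, so at that date it could still be settled before analysis. The downside is fewer significance claims for factors.

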## Appendix

Multimedia Appendix 1 Patient flowchart.

Multimedia Appendix 2 Assent to participate in the study.

Multimedia Appendix 3 Consent to participate in the study.

Multimedia Appendix 4 Proforma for the ocular condition.

Multimedia Appendix 5 Format of SMS texts and phone calls.

## Abbreviations

BEH: Bharatpur Eye Hospital
ERB: Ethical Review Board
OPD: Outpatient Department
